### 2.5. Recruitment

Participants will be prospectively included and compared with historical controls from the same sites. Participants meeting all the inclusion and not any of the exclusion criteria will be offered to start on the HR^35^ZE arm. After 8 weeks, participants will be managed according to the national TB guidelines.

The selected retrospective participants will provide a comparison for the primary safety outcome, and to the secondary efficacy outcome of culture conversion at 8 weeks using MGIT media. 

We adhered to all Pockock’s principles for historical controls except for the use of information from participants that were previously randomized in clinical trials [23]. To avoid the selection bias that may arise because of this limitation, we aim to include all adult patients fulfilling the inclusion criteria treated with HR^10^ZE in the participating sites between January 2017 and December 2019 (to avoid the influence of the 2020–2021 SARS-CoV-2 pandemic in TB diagnoses and follow-up). Thus, the records of all patients from that period with pulmonary and extrapulmonary rifampicin susceptible tuberculosis will be reviewed. We will capture the severe or grade 3 adverse events and week 8 microbiological status from those who are ≥60 years, or ≥18 years and have a diagnosis of diabetes, malnutrition, HIV, HBV or HCV coinfection, other stable chronic liver diseases, or TB meningitis, and have no pharmacological immunosuppression. We intend to control the retrospective cohort to match the prospective one for age, sex, cavitation in lung TB, and severity in TB meningitis. In case not enough matched controls are not found, we will extend the search with patients until the calculated sample size in the control arm is achieved. The historical cohort will include participants from only Spain, Portugal, and Paraguay and not likely from the Netherlands, as optimized doses of rifampicin have been used in both Dutch sites for more than a decade in the same participant subgroups as included in our study.

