## Abstract

Previous clinical trials for drug-susceptible tuberculosis (DS-TB) have shown that first-line treatment with doses of rifampicin up to 40 mg/kg are safe and increase the early treatment response for young adults with pulmonary tuberculosis. This may lead to a shorter treatment duration for those persons with TB and a good baseline prognosis, or increased treatment success for vulnerable subgroups (age > 60, diabetes, malnutrition, HIV, hepatitis B or hepatitis C coinfection, TB meningitis, stable chronic liver diseases). Here, we describe the design of a phase 2b/c clinical study under the hypothesis that rifampicin at 35 mg/kg is as safe for these vulnerable groups as for the participants included in previous clinical trials. RIAlta is an interventional, open-label, multicenter, prospective clinical study with matched historical controls comparing the standard DS-TB treatment (isoniazid, pyrazinamide, and ethambutol) with rifampicin at 35 mg/kg (HR^35^ZE group) vs. rifampicin at 10 mg/kg (historical HR^10^ZE group). The primary outcome is the incidence of grade ≥ 3 Adverse Events or Severe Adverse Events. A total of 134 participants will be prospectively included, and compared with historical matched controls with at least a 1:1 proportion. This will provide a power of 80% to detect non-inferiority with a margin of 8%. This study will provide important information for subgroups of patients that are more vulnerable to TB bad outcomes and/or treatment toxicity. Despite limitations such as non-randomized design and the use of historical controls, the results of this trial may inform the design of future more inclusive clinical trials, and improve the management of tuberculosis in subgroups of patients for whom scientific evidence is still scarce. Trial registration: EudraCT 2020-003146-36, NCT04768231.

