### 2.2. Objectives and Endpoints

The study primary objective is to evaluate the safety of high-dose rifampicin (35 mg/kg/d) as part of a standard first line regimen using standard doses of isoniazid (5 mg/kg), pyrazinamide (25 mg/kg), and ethambutol (15–25 mg/kg) for 8 weeks in adult subjects with pulmonary or extrapulmonary DS-TB belonging to difficult to treat subgroups. The secondary objectives are to evaluate the tolerability, efficacy, bactericidal activity, pharmacokinetic/pharmacodynamics, and cost effectiveness of high dose rifampicin, among others. 

The primary safety endpoint is the proportion of participants and historical controls with one or more grade 3 or higher adverse events (AE) according to the CTCAE v5 or SAE at 8-weeks after treatment with high-dose rifampicin onset. Table 2 below describes in detail the analysis population and primary safety outcomes. The secondary tolerability endpoint includes the proportion of participants with any AE. The secondary efficacy endpoint includes the proportion of participants and historical controls who have sputum culture conversion at 8 weeks after treatment onset or a proportion of participants with clinical improvement according to the treating physician (if follow-up images are available for extra-pulmonary TB) but without a follow up sample at 8 weeks after treatment onset.

Most TB phase 2 trials complete their intervention at week 8 or earlier and then participant care is transferred to a public institution within the National TB programs, so the information about end of treatment and post-treatment outcomes is scarce [10,17,18]. In the RIAlta trial, after the intervention and the primary safety objective evaluation, an extended follow-up period will be offered to participants, in line with the phase 2b/c design suggested by Phillips et al. [19]. This will provide information about end-of-treatment outcomes and relapse incidence in the prospective group.

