### 2.4. Study Population and Eligibility 

Adult participants ≥18 years with confirmed or probable pulmonary or extrapulmonary TB will be eligible to participate in the study. Additionally, trial candidates must be older than 60 years or have one of the following: diabetes, HIV, HBV or HCV coinfection, malnutrition (body mass index below 18.5 kg/m^2^), or any other chronic but stable liver disease. 

Adult participants with *M. tuberculosis* that is rifampicin-resistant by Xpert MTB/RIF or by drug susceptibility testing; with a Barthel index < 40 or life expectancy of less than 2 months regardless of anti-TB treatment; with signs of hepatotoxicity characterized by AST or ALT > 5x upper limit of normal, total bilirubin > 3x upper limit of normal, Child–Pugh grade C cirrhosis or acute decompensation at enrollment, or any grade 3–4 hepatobiliary alteration; who were previously treated with first-line anti-TB drugs or quinolones for at least 14 days or current treatment for more than 7 days; with solid organ or bone marrow transplantation; with active neoplasm requiring chemotherapy or immunotherapy treatment; or with previous severe pulmonary disease other than TB according to the investigator’s judgment will be excluded from the study. Participants with aischemic heart disease OR severe arrhythmia within 6 months OR subjects with atrial fibrillation and indication of oral anticoagulant therapy when transitioning to low-molecular weight heparin is not feasible will also be excluded from the study. Lastly, pregnant or breastfeeding women and participants not suitable to be included according to the investigator will not be enrolled for the study.

This is one the key differential aspects of RIAlta’s design. Previous trials have included people living with HIV, but few participants with diabetes, age over 60, or chronic liver disease were included [11,22].

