### 2.6. Intervention

The intervention in this study is a once daily high-dose of rifampicin at 35 mg/kg. A dose-finding study conducted in South Africa found that 40 mg/kg/day was the maximum tolerated dose in young participants without significant comorbidities [8]. Participants should start anti-TB treatment as soon as possible after signing written informed consent. This protocol allows a window of up to 7 days to complete screening tests (whether TB treatment was initiated or not; see study design diagram: Figure 1). Pyridoxine (vitamin B6) supplementation will be allowed as per local guidelines recommendations. The investigation team will carefully assess other concomitant drugs. When interactions are detected, dose adjustments or substitutions by an alternative drug will be at the discretion of the investigators.

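### Historical controls are not stated to meet the same entry rules or time zero as participants, which can bias the primary safety comparison in a direction the article does not settle

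*Protocol article*

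**What the plan says.** **Participants.** Section 2.4 admits adults with confirmed or probable TB who also have a risk factor: "trial candidates must be older than 60 years or have one of the following: diabetes, HIV, HBV or HCV coinfection, malnutrition", or another stable chronic liver disease. TB meningitis is not on this list. A long set of exclusions follows, including people "with a Barthel index < 40 or life expectancy of less than 2 months regardless of anti-TB treatment", raised liver enzymes or bilirubin, Child-Pugh C or decompensated cirrhosis, transplantation, neoplasm under chemotherapy or immunotherapy, severe lung disease, recent cardiac disease and pregnancy. Section 2.5 confirms that participants must pass both the inclusion and the exclusion lists.

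**Controls.** In the same section the sponsor writes "we aim to include all adult patients fulfilling the inclusion criteria treated with" the standard regimen at the sites from 2017 to 2019, and offers this as protection against selection bias. The filter is rifampicin-susceptible TB, age 60 or more or a listed condition, and it ends "other stable chronic liver diseases, or TB meningitis, and have no pharmacological immunosuppression". No other exclusion is named.

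**TB meningitis.** The Abstract counts it among the vulnerable subgroups: "HIV, hepatitis B or hepatitis C coinfection, TB meningitis, stable chronic liver diseases". Section 2.5 also matches on its severity.

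**Time zero.** The safety endpoint in section 2.2 is read "8-weeks after treatment with high-dose rifampicin onset". Section 2.4 tolerates up to 7 days of current TB treatment at entry, and section 2.6 "allows a window of up to 7 days to complete screening tests (whether TB treatment was initiated or not". For both groups, section 2.10 counts 8 weeks from the start of experimental treatment, which controls never receive.

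**Matching.** Section 2.5 lists age, sex, cavitation and TB meningitis severity. If matches run short, the search is extended until the sample size is reached.

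**The concern.** The controls are the only comparator for the primary safety claim, so any difference in who may enter passes directly into the estimated difference. Followed as written, a very frail patient, one close to death or one with marked liver injury at baseline can be a control but not a participant.

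The endpoint in section 2.10 makes this matter. Besides rifampicin-related events of grade 3 or higher, it counts treatment not completed for other reasons and loss to follow-up. A control who was dying at baseline can therefore be an event without any link to rifampicin. The excluded life expectancy (under 2 months) is almost the same length as the 8-week window.

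The undefined control start adds a second possible asymmetry. A participant who has already taken several days of treatment has survived and tolerated those days before the safety window opens. Whether the same holds for a control cannot be told.

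Both mechanisms could raise the control event rate relative to the participants' rate, and so make a more toxic regimen look non-inferior.

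**Working it through.** **Step 1. The entry rules side by side (sections 2.4 and 2.5).**

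| Rule | Participants | Controls |
|---|---|---|
| Criteria applied | Inclusion and exclusion | Inclusion named; exclusions not stated |
| TB meningitis alone qualifies | Not listed | Yes |
| Pharmacological immunosuppression | Not itself an exclusion | Barred |
| Age criterion | Older than 60 | 60 or older |
| Start of safety window | High-dose rifampicin onset, after 0-7 days of treatment | Undefined |

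Matching does not cover comorbidity, liver status, functional status or cardiac disease, so it cannot restore the missing exclusions. The extended search weakens it further.

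**Step 2. The plan's sample size.** Section 2.9 gives 134 per arm with an 8-point margin, alpha 0.1, power 0.8, 5% not assessable, and expected rates of 5-10% (mean 8%). With n = 2p(1-p)(z_alpha + z_power)^2 / 0.08^2, p = 0.10 and one-sided alpha 0.10, n = 126.8, rounded up to 127. Then 127/0.95 = 134. At the stated mean of 8% the same formula gives 104, or 110 with the 5% allowance. I use 134 below only as the number analysed per arm.

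**Step 3. Effect of control inflation (illustration).** From the article: the 8-point margin, the 95% CI rule (sections 2.8 and 2.10) and 134 per arm. Assumed: a true comparable control rate of 8% and a true HR35ZE rate of 16%, so the real excess equals the margin. Let b be the change in the observed control rate caused by different entry rules or recording, and p_c = 0.08 + b.

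SE = sqrt{[p_c(1-p_c) + 0.16 × 0.84]/134}

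P(declare non-inferiority) = Φ{[0.08 - (0.16 - p_c)]/SE - 1.96}

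For b = 0.02: SE = sqrt[(0.0900 + 0.1344)/134] = 0.0409, and Φ(0.02/0.0409 - 1.96) = Φ(-1.47) = 7.1%.

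| b (points) | False non-inferiority |
|---|---|
| -2 | 0.6% |
| 0 | 2.5% |
| +1 | 4.4% |
| +2 | 7.1% |
| +3 | 10.8% |
| +4 | 15.5% |

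**Step 4. What would produce b of 1 to 4 points.** If a share f of controls would fail participant entry and has event rate r, then b = f(r - 0.08). With an assumed r of 30%, b = 1 needs f = 1/22 = 4.5% and b = 4 needs f = 4/22 = 18%. The article gives neither f nor r.

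**Step 5. The opposite direction.** If control events are under-recorded by 2 points and the arms are truly equal at 8%, the chance of showing non-inferiority falls from 67.5% to 48.7%. (That 67.5% is below the planned 80% is a separate matter.)

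**The case against.** The best defence has five parts.

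- **Silence is not a waiver.** A reader might infer that the exclusions are not applied to controls. The article says only that controls fulfil the inclusion criteria, and a fuller protocol exists. Some exclusions also carry over in substance: rifampicin susceptibility, liver disease described as stable, and no immunosuppression (which overlaps transplantation and much chemotherapy). This stands as a limit on the claim. However, section 2.5 uses two different formulas for the two cohorts within one section and presents the control filter as its safeguard against selection bias, so the gap needs closing.
- **TB meningitis may be a slip in section 2.4.** The Abstract and the matching on severity both presuppose participants with meningitis, and extrapulmonary TB is admitted. Matching on severity would limit a surplus among controls. This is plausible, but the text still contradicts itself.
- **The control clock is undefined, not shown to differ.** A reader might infer that controls are followed from the first dose of the standard regimen and that first-week events count only for them. The article states no such start, and participants untreated at entry do have their first week counted.
- **The week-8 culture.** A reader might also infer that participants gain an extra week before it. Section 2.2 counts conversion from treatment onset in both groups, so the documents do not support this.
- **Direction.** Section 3 says that control events were not systematically collected, and immunosuppressed patients are barred from controls only. Both could lower the control rate. One committee also reviews relatedness in both cohorts (section 2.8). This stands: the net direction is unknown. Under-recording of unknown size is still no safeguard, and it is less plausible for deaths and non-completion than for graded laboratory or clinical events.

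**Conclusion.** The point holds as a mismatch in stated rules that can bias the primary comparison. It does not hold as proof that control events are inflated. The article states different entry rules for the two cohorts, contradicts itself on the status of TB meningitis, and leaves the controls' time zero undefined. Because non-completion and loss to follow-up count as events, these gaps can raise the control rate and favour non-inferiority. The stronger conclusion, that the design is tilted towards declaring high-dose rifampicin safe, is not supported, because incomplete recording and the control-only bar on immunosuppression may act the other way.

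The size is illustrative: 1 to 4 points of inflation would take false non-inferiority from 2.5% to about 4-16%. This rests on assumed true rates of 8% and 16%, 134 analysed per arm, a two-sided 95% CI and the normal approximation. The article gives no figure for the share of controls who would fail participant entry, or for their event rate.

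Sections 2.15 and 3 acknowledge that the design is prone to bias. That does not excuse this part, which can be avoided before control records are extracted.

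**What to change.** 1. Apply the section 2.4 inclusion and exclusion criteria to both cohorts, as far as charts at treatment start can show them. State which criteria cannot be recovered from records.
2. Use the same rule on pharmacological immunosuppression and the same age cut-off in both cohorts.
3. Reconcile the Abstract and sections 2.4 and 2.5 on TB meningitis, so that it has the same status as a qualifying condition in both cohorts.
4. Define one comparable time zero for the 8-week safety window that accounts for treatment days before enrolment. One option is to start each control's window after the same number of treatment days (0 to 7) as its matched participant had, with eligibility judged on that day. Replace the reference to experimental treatment start in section 2.10 accordingly.

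The cost is protocol wording, a few more chart variables and somewhat fewer eligible controls. It does not cure incomplete recording of control events, which remains a limitation to report.

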### 2.8. Assessment of Study Outcomes, Analysis Groups, and Duration of Follow-Up

The primary safety hypothesis is that the incidence of adverse events in the high dose rifampicin (35 mg/kg) supplemented with isoniazid, pyrazinamide, and ethambutol [HR^35^ZE] during the first 8 weeks of treatment will not exceed that of controls on a standard HRZE regimen (rifampicin 10 mg/kg) [HR^10^ZE]. The HR^35^ZE regimen will be considered unsafe if in a non-inferiority analysis, the upper limit of the 95% confidence interval of the difference of proportions in grade ≥ 3 AE (according to CTCAE scale version 5) between the experimental and the historical control arm exceeds 8%. The most common adverse events related to therapy with higher rifampicin doses were vomiting, headache, hyperuricemia, pain in the extremities, and pruritus. No significant differences according to rifampicin dose (from 10 to 35 mg/kg) were found in a recent systematic review and in a retrospective study collecting the real-life experience from a Dutch center [24,25].

To assess the AE and ensure a homogeneous evaluation of their grade, severity, expectedness, and treatment relatedness, we will administer a standardized training for the investigators from all different sites. In addition, both for the prospective and the retrospective cohorts, grade 3 or higher adverse events and SAE will be reviewed by the trial’s Steering Committee for relatedness classification. When no consensus is reached, the Data and Safety Monitoring Board formed by experts independent from the trial will make the final decision.

Tolerability will be measured as any adverse event (grade 1 to 4), treatment dropout rate, and any dose reduction. For efficacy outcome, the hypothesis is that in DS-TB participants (pulmonary disease), the proportion of participants experiencing successful treatment outcomes (culture and smear negative) at the end of the intensive phase of treatment on HR^35^ZE will be non-inferior to that of controls on HR^10^ZE. The HR^35^ZE regimen will be considered ineffective if the lower limit of the 95% CI of the proportion of participants with a negative sputum culture (sputum sterilization), or unable to produce sputum if they have a previous negative culture at week 8, is more than 10% lower than that of historical controls treated with HR^10^ZE. Other exploratory outcomes will be reported descriptively. 

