### 2.9. Sample Size Assumptions and Justification

For the sample size calculation, a non-inferiority design is assumed and the upper limit of the 95% confidence interval (CI) of the difference of proportions in grade 3 or higher adverse events at 8 percentage points has been set. We assume that 5% of patients will not be assessable. Alpha risk is set in 0.1 and power in 0.8. Based on the previous literature and our previous experience, expected standard treatment grade ≥ 3 AE are 5–10% (mean 8%) among experimental arms and standard treatment arms. Considering this, the number of participants per arm has been calculated to be 134 participants. Because of the limited recruitment capacity for this trial, we could not target specific numbers of participants for each sub-group of risk factors. 

Based on a feasibility survey performed at the planning stage, the target enrollment rates per country were: Paraguay 6.25 participants per month; Spain, Portugal, and the Netherlands 1.6 participants per month.

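### The rules for forming the historical control arm do not define one set of patients, and nothing in them keeps the choice of controls apart from the outcomes

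*Protocol article*

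**What the plan says.** Section 2.5 (Recruitment) makes four statements about the control arm.

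- To limit selection bias, the aim is to include all adults meeting the criteria who were treated with the standard regimen at the sites from January 2017 to December 2019.
- Outcomes are collected by eligibility: "We will capture the severe or grade 3 adverse events and week 8 microbiological status from those who are ≥60 years", or who are adults with one of the listed conditions.
- A match is intended: "We intend to control the retrospective cohort to match the prospective one for age, sex, cavitation in lung TB, and severity in TB meningitis".
- If too few matched controls are found, the search is extended until the control arm reaches the calculated size. The direction of the extension is not given.

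The Abstract says participants will be "compared with historical matched controls with at least a 1:1 proportion". Section 2.9 gives the size: "the number of participants per arm has been calculated to be 134 participants". Section 2.8 calls the regimen unsafe if the upper limit of the 95% interval for the difference "between the experimental and the historical control arm exceeds 8" percentage points. It sets a 10-point rule for culture conversion against the same historical controls. Section 2.1 describes the prospective cohort as open label.

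**The concern.** Without randomisation, forming the control group takes the place of allocation. Three stated rules compete: take everyone, take a matched subset, or keep adding until a number is reached. If everyone is taken, matching and the ratio have no role. If a matched subset is taken, the protection offered by taking everyone is gone. The ratio has a floor but no fixed value.

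Two features make this more than a wording problem. Adverse events and week 8 status are gathered for the eligible pool, not only for those selected. Matching to the prospective cohort cannot be finished until that cohort is known, and its outcomes are open. Nothing described separates the choice of controls from the outcome data. If outcomes did influence the choice, even unintentionally, the control event rate would be partly selected. Later covariate adjustment or adjudication of events could not undo that. Both the safety and the culture comparisons use these controls; only the safety comparison is quantified below.

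**Working it through.** **Inputs.** From section 2.9: 134 per arm; "Alpha risk is set in 0.1 and power in 0.8"; "expected standard treatment grade ≥ 3 AE are 5–10% (mean 8%) among experimental arms and standard treatment arms"; "We assume that 5% of patients will not be assessable". From section 2.8: a margin of 8 points and a 95% interval for the difference.

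**The plan's own figure.** n per arm = 2p(1−p)(z_α + z_β)² / 0.08², divided by 0.95 for the non-assessable.

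- p = 10%, one-sided alpha 0.10, power 0.80: n = 126.8, rounded up to 127; 127/0.95 = 133.7, so 134. This reproduces the plan.
- p = 8%, the stated mean, with the same alpha: 104, then 110. With one-sided alpha 0.05: 143, then 151. With 0.025: 181, then 191. None gives 134.

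That mismatch is a separate matter. The 134 is used below as stated.

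**One control near the boundary.** Upper limit = p₁ − p₂ + 1.96 √[p₁(1−p₁)/n₁ + p₂(1−p₂)/n₂].

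| Treated | Control | Difference | Standard error | Upper limit | Against 8 points |
|---|---|---|---|---|---|
| 13/134 | 11/134 | 1.49 | 3.49 | 8.33 | fails |
| 13/134 | 12/134 | 0.75 | 3.55 | 7.71 | passes |
| 13/134 | 22/268 | 1.49 | 3.06 | 7.49 | passes |

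Difference, standard error and limit are in percentage points. Rows one and two differ by one control with an event in place of one without. Rows one and three have the same control rate, and only the ratio changes.

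The one-control flip does not depend on the Wald interval. Newcombe limits are 8.64 and 7.99 for rows one and two. With a 90% interval, 14 versus 11 gives 8.08 (fails) and 14 versus 12 gives 7.44 (passes). Section 2.10 words the rule differently, setting the upper bound of the treated proportion against the control estimate plus 8 points. Under that rule, 14 treated events have an exact upper bound of 16.91%. The threshold is 16.21% with 11 control events (fails) and 16.96% with 12 (passes).

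**How often one control decides.** These figures come from exact binomial enumeration with 134 per arm, the Wald 95% rule and 8% in both arms. The chance of passing is 67.8%. It is 74.0% with one control event added and 61.1% with one removed. So 74.0 − 67.8 = 6.2% of trials would move from fail to pass, and 67.8 − 61.1 = 6.6% (from unrounded values) from pass to fail. Together that is about 13%.

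**Effect on error rates.** Here k control slots hold an event instead of a non-event.

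| True rates (treated, control) | k | Chance of declaring non-inferiority |
|---|---|---|
| 16%, 8% | 0 | 2.9% |
| 16%, 8% | +1 | 4.2% |
| 16%, 8% | +3 | 7.9% |
| 16%, 8% | +4 | 10.6% |
| 8%, 8% | 0 | 68% |
| 8%, 8% | −4 | 41% |

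**Effect of the open ratio.** This assumes a pool of 268 exchangeable eligible controls; the article gives no pool size. Taking the most favourable of two 1:1 sets and the full 2:1 set raises false non-inferiority at 16% versus 8% from 2.9% to 5.2% by simulation.

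**The case against.** The strongest reply is that section 2.5 already contains the safeguard. If all eligible 2017–2019 patients enter, nobody chooses among records, and a ratio of at least 1:1 simply describes what a closed calendar pool yields. This would settle the matter if the aim stood alone. It does not, because the same paragraph goes on to matching and to a size-driven extension.

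A reader might infer that controls will in fact be picked with outcomes in view. The documents do not support that. They do not say who matches, when, or what that person can see, and the order of sentences in an article is not an order of operations. Nor do they show a surplus of candidates per participant: no pool size is given, and the only contingency described is a shortage.

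Three further points stand in part.

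- Algorithms, calipers and masking may sit in the full protocol or analysis plan, so their absence here is not a fault. The conflict between the stated rules is.
- Relatedness of events in both cohorts is classified by the Steering Committee, with the independent board deciding when there is no consensus (section 2.8). A record reviewer therefore does not hold the final endpoint, although raw events could still be visible.
- Any threshold rule turns on one event at its boundary, so the 13-event example is an illustration.

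Sections 2.15 and 3 disclose that the non-randomised design is open to bias. That disclosure does not say which controls will be used.

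**Conclusion.** The point holds as a defect in how the control arm is fixed. The article's rules do not determine one control set, the ratio is open, and nothing stated prevents selection after outcomes are known. It does not show that such selection is planned or likely.

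The size is moderate. At the design rates there is about a 13% chance that one control decides the result. At a true difference equal to the margin, one outcome-driven swap adds 1.3 percentage points to the false non-inferiority rate (4.2 − 2.9). Four swaps add 7.7 (10.6 − 2.9), but that number of swaps is chosen for illustration and has no basis in the documents. The figures assume 134 evaluable patients per arm, independent binomial outcomes and an unadjusted Wald 95% interval. A matched or adjusted analysis would change the values. The remedy is cheap enough that the change should be made.

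**What to change.** State one rule for the control arm. Either include all eligible controls, with weights or adjustment fixed from baseline data, or use a programmed match at a preset ratio, with a fixed seed and a stated fallback for when matches run short.

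Whichever is chosen, first extract only eligibility and matching variables into a baseline-only file. Build and lock the control list from that file, and merge the adverse event and week 8 culture fields only afterwards. Allow no replacement of a control after the merge.

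The cost is protocol or data-management wording and a change in the order in which fields are released. No extra patients or staff are needed. The small downside is that the ratio cannot be changed later.
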